## Abstract

Callous–unemotional (CU) traits are associated with specific cognitive and emotional deficits, which help explain their severe aggressive behavior. In the ICD-11/DSM-5, CU traits have been added to the diagnostic criteria for disruptive behavior disorder (DBD) as the “limited prosocial emotions” (LPE) specifier. The semi-structured Clinical Assessment of Prosocial Emotions (CAPE) interview is a new method to identify LPE. This study protocol describes the German translation of the semi-structured CAPE and the planned evaluation of its construct validity in a clinical sample of children diagnosed with DBD in Germany. Given that individuals with elevated CU traits can be categorized into primary (less anxiety, with less experience of abuse) and secondary (high anxiety, with more experience of abuse) variants, this study protocol will outline the planned exploratory analysis of these variants in a German clinical sample. The research questions will be examined in a multicenter, cross-sectional, clinical observational study using a case–control design. The study will include children and adolescents aged 8–18 and their primary caregivers. Multivariable general linear models will be used to assess the construct validity of CAPE and to explore differences between CU trait variants. Validating a German version of CAPE could provide clinicians and researchers with a standardized tool to assess LPE, enabling treatment tailored to CU trait variants. Trial Registration: German Clinical Trials Register, DRKS00035428, registered on 5 November 2024. Ethical approval was obtained from the Friedrich-Alexander Universität Erlangen-Nürnberg (reference number: 24-112-S) on 28 May 2024. Trial status: Recruiting ongoing.

## 1. Introduction

Disruptive behavior disorder (DBD) is a pattern of symptoms that is characterized by oppositional and aggressive behavior that restricts the fundamental rights of others. DBD has been linked to delinquency, substance abuse, criminality, and low educational achievement in children and adolescents (Hyde et al., 2026; Odgers et al., 2007). Given the considerable harm inflicted on society and individuals (Burt et al., 2018), research has identified a high-risk group with callous–unemotional traits (CU traits) and DBD. They are defined by four criteria: a lack of remorse or guilt, a lack of empathy, unconcern about performance, and shallow or deficient affections (Frick et al., 2014).

Children exhibiting CU traits demonstrate substantial impairments in neurocognitive and social–emotional processes, encompassing response inhibition, emotion recognition, response to reward and punishment cues, and affective empathy (Díaz-Vázquez et al., 2024; Fanti et al., 2024; Frick & Kemp, 2021; Hyde et al., 2024; Kimonis et al., 2023; Viding et al., 2012). In earlier studies, children with CU traits showed more persistent and aggressive behavior, had more police contacts over time, showed more antisocial behavior, were more likely to engage in bullying, and proactively used aggressive behavior to achieve their goals compared to unaffected peers (Catone et al., 2021; Frick et al., 2003, 2005; McDonough-Caplan & Beauchaine, 2018; Muñoz & Frick, 2012; Olivera-La Rosa et al., 2023).

Consequently, the presence of CU traits in children with DBD is indicated by the specifier “with limited prosocial emotions” (LPE) in the ICD-11 and DSM-5 (American Psychiatric Association, 2013; Frick et al., 2014). In case of a patient diagnosed with DBD, a specific LPE may be assigned if two CU traits—for example, lack of remorse and guilt, and shallow or deficient affection—persist for longer than one year. Approximately half the children with DBD exhibit elevated levels of CU traits (Kahn et al., 2012; Pisano et al., 2017). In analyses of risk factors for the development of CU traits, research has identified associations between parental characteristics (i.e., low parental warmth, harsh parenting, and parental psychopathology) and an increased likelihood of CU traits in their offspring (Frick & Viding, 2009; Waller et al., 2015, 2017; Wright et al., 2018). Children from families of low socioeconomic status and those from parents with adverse childhood experiences have been linked to higher levels of CU traits, while parental warmth in parenting has been identified as a protective factor (Hyde et al., 2016; Kohlhoff et al., 2020; Pueyo et al., 2022; Tomlinson et al., 2022; Waller et al., 2015).

From a longitudinal perspective, the focus has been on CU traits that develop in response to an earlier traumatic experience (secondary CU traits). A meta-analysis revealed a low to medium correlation between childhood maltreatment experiences and the development of CU traits (Todorov et al., 2023). In this context, CU traits are regarded as survival strategies following traumatic childhood experiences, especially experiences of abuse. The pervasiveness of victimization experiences among individuals characterized by high secondary CU traits may provide a rationale for the consistent lack of moral maturity (Eilts & Bäker, 2024; Kimonis, 2023). This would stand in contrast to primary CU traits, in which traumatic experiences are less prevalent, and deficits in emotion recognition and affective empathy prevail. Studies have shown differences between children and adolescents with primary versus secondary CU traits in aggressive behavior, i.e., proactive aggression in primary CU traits versus reactive aggression in secondary CU traits: In addition, secondary CU traits are associated with elevated scores in CU traits, depression, anxiety, and attention problems (Bennett & Kerig, 2014; Craig et al., 2021; Craig & Moretti, 2019; Dadds et al., 2018; Kahn et al., 2013; Kimonis et al., 2012; Mozley et al., 2018; Vasileva et al., 2019). However, studies on primary and secondary CU traits have rarely addressed traumatic events and have predominantly been based on anxiety intensity (Craig et al., 2021).

### 1.1. Previous Literature and Rationale

To address these open research questions, a valid measurement of CU traits and their subtypes is crucial. CU traits are typically assessed using questionnaires such as the Antisocial Process Screening Device (APSD; (Frick & Hare, 2001)) or the Psychopathy Checklist (PCL-R; (Hare, 2003)). In this context, the Inventory of Callous–Unemotional Traits (ICU (Frick, 2004)) is the current gold standard, characterized by its medium to high test quality (Cardinale & Marsh, 2020) and tripartite subscale structure (callousness, uncaring, and unemotional) (Bhanwer et al., 2019; Fanti et al., 2009; Kimonis et al., 2008, 2015). The merits of the three-factor model structure have also been confirmed in the German version of the child and adolescent self-report (ages 6–18) (Essau et al., 2006). In a clinical German sample, a three-factor model (Callousness/Lack of Guilt, Unemotional, and Unconcerned about Performance) has proven to be the best model fit. However, only Callousness/Lack of Guilt was associated with aggressive/antisocial behavior (Benesch et al., 2014).

Current questionnaires do not facilitate the evaluation of each CU trait individually to diagnose LPE and do not provide clinicians with direct feedback on potential treatment adjustments. This shortcoming contributes to the challenges in developing effective interventions. To address this gap, Frick developed the Clinical Assessment of Prosocial Emotions (CAPE) (Frick, 2013), which is oriented on the DSM-5 criteria of LPE. This semi-structured, thirty-minute clinical interview combines external judgment (from the primary caregiver) with self-judgment (from the child/adolescent). The CAPE was developed to provide a comprehensive assessment of CU traits and to serve as a structured professional judgment (SPJ) tool for diagnosing LPE. Each question is followed by several follow-up questions designed to assess the persistence and frequency of LPE symptoms. The semi-structured CAPE interview requires clinicians to collect specific examples to ascertain whether such behaviors occur across different situations and relationships. This enables us to identify a particularly vulnerable group that requires specialized care.

Within the group of CU traits, a distinction has been demonstrated between two types. However, definitions of primary and secondary CU traits diverge. In particular, the question of the extent to which traumatic experiences (Craig et al., 2021; Kimonis, 2023) and anxiety symptoms (Todorov et al., 2025) contribute to distinguishing the two subtypes is of particular interest. The concept can be traced back to Karpman’s (1941) seminal work, in which he posited that the core of secondary CU traits comprises internalizing symptoms, such as anxiety and depression, in response to a neglectful, unloving, or abusive environment. Porter (1996) expanded on this, referring to severe traumatic experiences in which CU traits are developed as a coping strategy to shut down. The present study protocol will follow this approach and examine both significant potentially traumatic events as well as high anxiety scores in the differentiation process. This is of particular significance given the evidence that children exhibiting secondary CU traits demonstrate a notably diminished response to treatment over time (Fleming et al., 2023). Furthermore, parents encounter a significantly greater challenge in expressing parental warmth (Kaouar et al., 2024) and may necessitate an adapted form of treatment (Kimonis, 2023). In order to achieve this objective, it is necessary to comprehend both primary and secondary CU traits by integrating the two approaches (trauma and anxiety).

### 1.2. Study Aims and Research Questions

Interview formats have proven more effective than current questionnaires for identifying CU traits because the practicing clinician receives direct feedback on which CU characteristics are present. Interviews are the key element for intervention planning. For this objective, the CAPE interview appears to be an appropriate instrument. Unfortunately, neither a German version nor an empirical assessment of the CAPE interview is currently available.

**Research question 1: Can Limited Prosocial Emotions (LPE) be validly diagnosed in a German clinical sample using a German version of CAPE?**

The validity of the CAPE interview data will be examined by correlating it with standardized questionnaire scores on CU traits, DBD, social competence, reactive/proactive aggressive behavior, empathy, emotion recognition, and parental warmth. Furthermore, groups are formed in which children with and without LPE are separated, allowing symptom severity and characteristics to be differentiated. The study at hand will examine the hypothesis that the CAPE is a superior instrument for predicting DBD, social competence, empathy, and emotion recognition compared with questionnaires.

Research has shown that a distinction between primary and secondary CU traits is important. The secondary CU traits result from children’s exposure to one or more traumatic events. This distinction has not previously been examined in a clinical sample from German-speaking countries. This leads to the following exploratory research question:

**Research question 2: Can primary and secondary CU traits be differentiated in a German clinical sample?**

Children diagnosed with DBD and elevated CU traits will be divided into two distinct groups: those with a history of traumatic experiences, i.e., two or more potentially traumatic experiences (secondary), and high anxiety (secondary), compared to those with less and lower anxiety (primary). The objective of this study is to examine the construct of primary and secondary CU traits using standardized procedures. The final two groups will be compared with respect to traumatic events, CU traits, DBD, reactive aggressive behavior, emotion recognition, parental warmth/strictness, attention problems, depression, and anxiety symptoms.

### 1.3. Working Hypotheses

**Construct Validity of CAPE and LPE**

*Interrater reliability and prevalence*

1.The CAPE interviews are expected to demonstrate moderate to very good interrater reliability.2.It is expected that approximately 50% of children diagnosed with DBD will also exhibit LPE.

*Convergent validity*

3.CAPE will be statistically significantly positively correlated with CU traits, DBD, (proactive) aggressive behavior, and parental strictness.

*Divergent validity*

4.CAPE will be statistically significantly negatively correlated with social competence, empathy, emotion recognition, and parental warmth.

*Incremental validity*

5.The CAPE Interview will demonstrate greater predictive validity than the ICU for DBD, social competence, (proactive) aggressive behavior, empathy, and emotion recognition.

*Group comparison of the specifier “with limited prosocial emotions”*

6.Children with an LPE will differ significantly and positively in CU trait expression, DBD, and (proactive) aggression compared to children without an LPE.7.Children with an LPE will differ significantly and negatively in social competence, empathy, emotion recognition, and parental warmth from children without an LPE.

**Primary and secondary CU traits**

Children with secondary CU traits will show significantly more severe symptoms of depression, attention problems, anxiety, CU traits, reactive aggressive behavior, parental strictness, and DBD than those with primary CU traits.Children with secondary CU traits will be better at recognizing emotions than children with primary CU traits.Children with primary CU traits will have parents who show more parental warmth than those of children with secondary CU traits.

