
Furthermore, it reduces the burden on participants and the organizational workload whilst also avoiding overlap in criteria with the child-report questionnaires. For data analysis, the dimensional and dichotomous (LPE yes/no) score will be used. Furthermore, the second, double-blind coder for interrater reliability will be thoroughly prepared to focus on CU traits and their specific characteristics. The secondary coder will have undergone training with one of the original assessors and completed at least two sessions with that assessor before coding CAPEs herself.

Primary caregiver- and child-rated

**CU Traits**: The *Inventory of Callous–Unemotional Traits* (ICU; 11 to 17 years (Frick, 2004)) is a 24-item self-report questionnaire. There are parent- and child-rated versions. A total score can be calculated. Higher scores suggest higher levels of CU traits.

**DBD and social competence:** The *Diagnostic System for Mental Disorders in Children and Adolescents* (DISYPS; 4 to 18 years; (Döpfner et al., 2017)) assesses diagnostic criteria for conduct problems according to ICD-10 and DSM-5 across 55 items. There are parent- and child-rated versions. A total score and six subtest scores (oppositional behavior, aggressive-dissocial behavior, limited prosocial emotions, disruptive affect regulation disorder & irritability, functional impairment, DBD score, and social competence) can be calculated. Higher scores suggest higher symptom levels.

Primary caregiver-rated

**Aggressive behavior, attention problems, physical complaints, depression, and anxiety**: The *Child Behavior Checklist* (*CBCL*; 6 to 18 years (Döpfner et al., 2014)) is a 119-item questionnaire for assessing emotional and behavioral problems in eight primary (anxious/depressed; withdrawn/depressed, physical complaints, social problems, thinking, sleep and repetitive problems, attention problems, rule-breaking behavior, aggressive behavior) and three secondary subscales: internal (anxious/depressed; withdrawn/depressed, physical complaints), external (rule-breaking behavior, aggressive behavior) and general problems (social problems, thinking, sleeping and repetitive problems, attention problems). Higher scores on the scales indicate behavior problems in this area.

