**For research question 2:**

*Defining groups*

Patients with ‘highly descriptive’ in at least one CU Trait on the CAPE interview will be separated into two groups (primary or secondary CU traits), theory-informed by the experience of two interpersonal potentially traumatic events (≥2 = secondary CU traits) and by anxiety scores (T ≥ 70 = secondary CU traits). This approach requires that the SPJ assessment include at least one CU characteristic, thereby ensuring that the exploratory subgrouping is limited to patients who exhibit clinically relevant CU-related characteristics. It is imperative to acknowledge that this exploratory classification does not aspire to represent or supersede a formal LPE classification. We concur with Cecil et al. (2018) that data-driven methodologies, such as cluster analysis, are not feasible in a clinical context, where decisions are made according to cutoff points. Moreover, previous analyses have demonstrated that trauma allows for a distinction between primary and secondary CU traits (Cecil et al., 2018; Kimonis et al., 2012), and there is also evidence that anxiety effectively differentiates between the two forms (Todorov et al., 2025). Consequently, we adhere to the recommendations set forth by Craig et al. (2021) and undertake a comprehensive assessment of potentially traumatic experiences and anxiety levels. In this study, a cutoff of two potentially traumatic experiences will be used to account for severity and to model repeated interpersonal trauma (Karpman, 1941; Kimonis et al., 2012; Pueyo et al., 2022).

*Group comparison*

ANCOVA models assessing group differences between primary and secondary CU trait groups across relevant constructs (CU traits, emotion recognition, reactive aggressive behavior, depression, attention problems, anxiety, parental warmth/strictness, and DBD) will be conducted. We will control for age, study site (waiting list, outpatient, daycare, or inpatient), and sex in the ANCOVA models.

*Effect size and statistical assumption*

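### Anxiety helps define the primary and secondary CU groups and is then tested as an outcome of that grouping, so a significant difference is no evidence that the variants can be differentiated

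*Protocol article*

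**What the plan says.** **Grouping (Section 2.6, research question 2).** Children rated highly descriptive on at least one CU trait are split by two cutoffs: "experience of two interpersonal potentially traumatic events (≥2 = secondary CU traits" and "by anxiety scores (T ≥ 70 = secondary CU traits". Section 1.2 words the split as trauma history "and high anxiety (secondary), compared to those with less and lower anxiety (primary".

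**Outcomes of the grouping.** Section 1.3 hypothesises: "Children with secondary CU traits will show significantly more severe symptoms of depression, attention problems, anxiety". The ANCOVA list in Section 2.6 reads "CU traits, emotion recognition, reactive aggressive behavior, depression, attention problems, anxiety, parental warmth/strictness, and DBD) will be conducted". The covariates are age, study site and sex. Section 1.2 adds: "The final two groups will be compared with respect to traumatic events, CU traits, DBD, reactive aggressive behavior"; the same sentence ends with anxiety symptoms.

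**Measures (Section 2.5).** The CBCL is the only anxiety instrument. Its internalising scales are given as "internal (anxious/depressed; withdrawn/depressed, physical complaints". The CATS-2 is the only event measure, scored as a count from 0 to 14.

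**Status.** Research question 2 is called exploratory. It nevertheless has directional hypotheses and its own sample size calculation in Section 2.4 (N = 84, raised to 101 for attrition).

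**The concern.** When a score is used to sort children into groups, a later test of that score between the groups mostly shows that the sorting took place. Research question 2 asks whether primary and secondary CU traits can be told apart in this sample. A cut on anxiety tends to produce an anxiety difference whether or not two variants exist.

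Nothing in the article breaks the loop. There is no second anxiety measure, the covariates do not remove the difference, and the comparison is nowhere called a check of the grouping. Section 1.4 says the distinction shows mainly in anxiety and abuse, which are the domains of the two classifiers, so a reader could take a significant anxiety result as support. For the CAPE ratings the plan does guard against circularity: Section 2.2 derives them independently of the questionnaires. Research question 2 has no such safeguard.

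**Working it through.** **1. The plan's own figure.** Two-group ANCOVA with f = 0.40, α = 0.05, power 0.95 (Section 2.4). Noncentral F with df1 = 1, df2 = N − 2 − covariates and noncentrality f²N. At N = 84 the noncentrality is 0.16 × 84 = 13.44. With three covariates the power is 0.952, and 84 is the smallest N reaching 0.95 with 0, 1, 3, 5 or 6 covariates. The figure reproduces. It is calculated per ANCOVA, so dropping one outcome does not change it.

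**2. What follows from the cutoffs alone.** If secondary means both criteria and primary means neither, every secondary child has T ≥ 70 and every primary child has T < 70. The T-score distributions cannot overlap, so the difference in means is certain before any data are seen. (Section 2.6 analyses total scores. Within one norm table T rises with the total, so the argument carries over; across norm tables slight overlap is possible.)

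The article does not settle this reading. Section 1.2 leans towards requiring both criteria, Section 2.6 attaches the secondary label to each cutoff separately, and the place of a child meeting only one is not stated.

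**3. Size under each reading.** These inputs are assumptions, not in the documents: anxiety T with mean 60 or 65, SD 10 and floor 50; Poisson event count with mean 1 or 2; anxiety-trauma correlation −0.3, 0 or 0.3. Each scenario used up to 1000 data sets of 84 children and an unadjusted t-test at two-sided 5%, counting rejections in the hypothesised direction. Data sets with fewer than three children in a group were dropped.

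| Reading | Correlation | Anxiety d | Anxiety rejected | Events d | Events rejected |
|---|---|---|---|---|---|
| Both v neither | −0.3 to 0.3 | 2.47–3.25 | 100% | 2.90–3.84 | 100% |
| Both v all others | 0 | 1.37–2.16 | 94–100% | 0.72–1.67 | 44–99% |
| Both v all others | −0.3 | 1.14–1.88 | 70–100% | 0.45–1.40 | 9–88% |
| Either v neither | 0 | 0.49–1.27 | 53–100% | 1.18–1.94 | 100% |
| Either v neither | −0.3 | 0.21–0.96 | 10–99% | 0.95–1.71 | 99–100% |

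A positive correlation of 0.3 gives larger differences than zero correlation in the two lower readings (anxiety d 1.63–2.47 and 0.79–1.62). A valid test with no true difference would reject in the hypothesised direction about 2.5% of the time.

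**4. Traumatic events.** This comparison appears in the Section 1.2 list, but not in the Section 1.3 hypotheses or the Section 2.6 ANCOVA list. The classifier counts interpersonal events, whereas the Section 2.5 score counts all 14. The two overlap but may not be identical, and the simulation treated them as one count.

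**5. Holm correction.** Suppose the family is the nine ANCOVA outcomes, counting warmth and strictness separately and one score per construct (an assumption). If anxiety is rejected first at 0.05/9 = 0.0056, the next test faces 0.05/8 = 0.00625. A family of eight without anxiety starts at the same 0.00625, so removing a certain rejection alters no other threshold.

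**The case against.** The best defence is that the article sets no rule by which the anxiety result decides research question 2. Most of the hypothesised outcomes lie outside the definition. Section 1.4 derives its expectations for reactive aggression, attention, strictness, warmth, emotion recognition and DBD, and Section 4 speaks of exploring depression, aggression and attention. The question is labelled exploratory, and Section 5 concedes that the variants are separated by cutoffs alone.

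This lowers the severity but does not answer the point. Anxiety remains a directional significance hypothesis and a listed ANCOVA outcome, and Section 5 does not say that a cutoff variable is also an outcome.

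Four stronger readings are tempting, and the documents do not support them:

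- *Traumatic events is a second circular hypothesis.* It is in the comparison list of Section 1.2 only.
- *Significance is guaranteed however the groups are formed.* Certainty follows only for both versus neither. In the weakest assumed case the anxiety test rejected about 10% of the time.
- *The depression outcome is circular too.* Section 2.5 lists a separate withdrawn/depressed scale, and the article does not say which scale is used. The overlap exists only if anxious/depressed items serve both purposes.
- *The anxiety test distorts the other tests through Holm.* It does not, relative to a family without it.

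**Conclusion.** The point holds for anxiety as a formal test, and for traumatic events as a comparison in Section 1.2. A significant difference on either is not evidence that the variants can be differentiated, because selection on the cutoffs produces or favours it.

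The anxiety difference is certain for both versus neither (simulated d about 2.5 to 3.3). Under the other two readings with no correlation, d is about 0.5 to 2.2. These sizes rest on the assumed distributions. That the classifier is reused as an outcome rests on the text alone, given that the CBCL is the only anxiety measure described. The severity is should-fix: the question is exploratory, but it has directional hypotheses, and its N of 84 is the basis of the target of 101.

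**What to change.** - Remove anxiety from the Section 1.3 hypothesis on secondary CU traits, from the research question 2 ANCOVA list in Section 2.6, and from the Holm family.
- Report anxiety and event counts only as a description of the groups, and reword the comparison sentence in Section 1.2 to match.
- State that the conclusion on research question 2 rests on outcomes external to the definition: emotion recognition, reactive aggression, parental warmth and strictness, attention problems, DBD and CU traits.
- If the CBCL anxious/depressed scale is the classifier, keep its items out of the depression outcome; the withdrawn/depressed scale is available.

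The cost is one formal test and a few lines of wording. N = 84 stays as it is. Recruitment is ongoing, so the change can be made before analysis.
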